## Abstract

**Background:**

Strong evidence supports beginning stroke rehabilitation as soon as the patient’s medical status has stabilized and continuing following discharge from acute care. However, adherence to rehabilitation treatments over the rehabilitation phase has been shown to be suboptimal.

**Objective:**

The aim of this study is to assess the impact of a telerehabilitation platform on stroke patients’ adherence to a rehabilitation plan and on their level of reintegration into normal social activities, in comparison with usual care. The primary outcome is patient adherence to stroke rehabilitation (up to 12 weeks), which is hypothesized to influence reintegration into normal living. Secondary outcomes for patients include functional recovery and independence, depression, adverse events related to telerehabilitation, use of services (up to 6 months), perception of interprofessional shared decision making, and quality of services received. Interprofessional collaboration as well as quality of interprofessional shared decision making will be measured with clinicians.

**Methods:**

In this interrupted time series with a convergent qualitative component, rehabilitation teams will be trained to develop rehabilitation treatment plans that engage the patient and family, while taking advantage of a telerehabilitation platform to deliver the treatment. The intervention will be comprised of 220 patients who will take part in stroke telerehabilitation with an interdisciplinary group of clinicians (telerehabilitation group) versus face-to-face standard of care (control group: n=110 patients).

**Results:**

Our Research Ethics Board approved the study in June 2020. Data collection for the control group is underway, with another year planned before we begin the intervention phase.

**Conclusions:**

This study will contribute to the minimization of both knowledge and practice gaps, while producing robust, in-depth data on the factors related to the effectiveness of telerehabilitation in a stroke rehabilitation continuum. Findings will inform best practice guidelines regarding telecare services and the provision of telerehabilitation, including recommendations for effective interdisciplinary collaboration regarding stroke rehabilitation.

**Trial Registration:**

ClinicalTrials.gov NCT04440215; https://clinicaltrials.gov/ct2/show/NCT04440215

**International Registered Report Identifier (IRRID):**

DERR1-10.2196/32134

## Introduction

Stroke impacts nearly 400,000 Canadians annually [1]. It is the leading cause of adulthood disability and is associated with substantial morbidity and mortality [2]. Three-quarters of stroke survivors will live with minor to severe impairments or disabilities, requiring rehabilitation services [3]. Strong evidence supports beginning rehabilitation as soon as the patient’s status has stabilized and continuing following discharge from acute care [4]. Returning home shortly after a stroke event places the patient in the most favorable environment to foster the success of the rehabilitation therapy [5] and should be favored over inpatient rehabilitation [6]. For this reason, enabling access and optimizing adherence to rehabilitation services is crucial to ensure positive patient and family outcomes [4]. That said, the need to travel long distances regularly to attend rehabilitation sessions with various professionals [7], the lack of coordination and communication among these outpatient services [4], and the failure to engage the patient and family members in a structured decision-making process [8] limit uptake and delivery of optimal services.

Telerehabilitation, which refers to the use of technology to provide long-distance rehabilitative services [9], is recommended by the Canadian Stroke Guidelines as a means to ensure equal and timely access to optimal stroke services [6]. In this research project, we focus on teletreatment, the provision of remote interprofessional rehabilitation and communication services using videoconferencing technologies.

Despite emerging evidence on the clinical and economic benefits of telerehabilitation [10,11], knowledge gaps remain, especially in a population of community-dwelling stroke patients [12]. Promising results following telerehabilitation include improved function [13-15] and recovery from motor deficits, social function [16,17], quality of life [18], and depression scores [16]. These studies, however, are often characterized by very small sample sizes (ie, fewer than 50 patients investigated), suboptimal treatment length (eg, 1-month duration, whereas guidelines recommend 8-12 weeks), or various definitions of what telerehabilitation entails [10,15,19-27]. As a result, many benefits of the intervention still need to be investigated using robust and large trials [12,14,28-32].

Furthermore, interprofessional shared decision making (SDM) has been shown to help teams to deliver better-quality care and resulted in significant improvements in patients’ rehabilitation process [33,34] (eg, patients’ knowledge and understanding, participation in the decision-making process, and satisfaction with and trust in the health care team). SDM refers to the process by which health decisions are deliberated upon and made jointly by the patient and one or more health professionals, taking into consideration the best available evidence and the patient’s values and preferences [35,36]. Although the effects of SDM have not been extensively documented [33,37] in stroke care, shared decisions are considered the crux of patient-centered care, and SDM has been correlated with greater adherence to treatment plans in other populations [38-43]. Structured interactions among team members through a telerehabilitation platform can create a unique opportunity to improve interprofessional communication and diagnosis skills by supporting the simultaneous participation of all team members, including the patients and family [43,44].

We propose a mixed methods clinical trial to assess the effectiveness of a telerehabilitation platform to increase adherence to rehabilitation stroke care as well as to increase patient participation in interprofessional SDM. The specific objectives of this project are to (1) evaluate the clinical, process, and cost outcomes of an interprofessional technology-enabled stroke rehabilitation intervention in comparison with usual care and (2) identify and describe key contextual factors related to the outcomes of this intervention.

## Methods

### Study Design

An interrupted time series design with a convergent qualitative component is proposed to test the effectiveness of the intervention. The intervention consists of observing the same dependent variable over time, with a break in the series of observations corresponding to the introduction of an intervention. If the intervention is effective, a change in the series’ pre- and postintervention averages can be observed [45]. Moreover, such design will accommodate pre-existing trends and control for possible variations within and among sites (eg, rehabilitation treatment efficacy, low adherence to treatment plan, and team composition). This study was registered at ClinicalTrials.gov (NCT04440215).

### Setting

Five selected sites in Quebec, Canada, will start with a control period (preintervention: usual care) until they independently reach their target sample size; this is expected to take between 12 and 18 months. Participants recruited during this period will belong to the control group. The sites will then enter the intervention period until recruitment completion, which is expected to occur after a further 12 to 18 months. Participants recruited during this second period will belong to the intervention group. Site monitoring will carefully document practices during both trial phases.

### Participants

The study population consists of male and female adults, 18 years and older, who (1) have had a stroke event, (2) are considered to be safe for home discharge by the acute or inpatient care team, (3) have a relative or caregiver who is present in the home should physical rehabilitation treatments be required, and (4) can speak French or English. Patients with severe cognitive decline prior to the stroke event will be excluded. Patients with communication difficulties resulting from the stroke event (eg, aphasia) will not be excluded. When possible, a patient’s relative or informal caregiver will also be recruited to document their experience of care. Inclusion and exclusion criteria will be similar to above with the exception of the stroke event [46].

Patients will be recruited at each rehabilitation center. At admission, the rehabilitation care coordinator will identify eligible patients and will present the study to the patients and their families. The consent form will be signed prior to the first intervention session. A research assistant will contact the patient and family by telephone to confirm consent and for data collection.

### Intervention

#### Control Phase

Rehabilitation teams will be instructed to provide care as they have been doing previously (ie, usual care). This translates into (1) no telerehabilitation, (2) interdisciplinary meetings not systematically organized and/or not involving a complete team of professionals, and (3) care plans not necessarily elaborated using interprofessional SDM principles.

#### Intervention Phase

The telerehabilitation platform will be installed at each site in rooms devoted to telerehabilitation activities and equipped with rehabilitation gears. The software OpenTera is a cloud-based multipoint, multi-view, and multi-stream (ie, video and audio) telecommunication system with proven usability and robustness for telerehabilitation applications [7]. The platform is not linked to a specific commercial platform or to special network configurations. It supports multisite interventions (ie, more than one patient at a time), making group sessions and interprofessional meetings feasible. A second camera will be installed on both clinician and patient kits for patients needing speech therapy. The rehabilitation team members will be trained to adapt rehabilitation exercises. Preintervention and ongoing training and coaching will be provided by a trainer who has extensive experience of training rehabilitation teams for various health care conditions; this will be done using the platform.

All rehabilitation teams will receive training in an interprofessional approach to SDM, which recognizes that multiple professionals may be involved in care planning and can support patients and their families in making decisions that are right for them. The teams will receive training to promote knowledge and skills on these topics, and sessions will be modeled after the interprofessional training program used successfully in two recent trials of SDM among home care teams [47,48]. The 3-hour program has two components: (1) a general online tutorial on SDM, based on the Ottawa Decision Support Tutorial [49], and (2) a skill-building workshop that includes a lecture, a video, and a role-play exercise. The brief lecture will be delivered by two experts in SDM and will provide definitions and a conceptual framework for the interprofessional SDM approach. The video will present a clinical vignette illustrating how the interprofessional SDM approach translates into a clinical scenario involving a patient and multiple professionals working together to collectively support a decision. The role-playing exercise will then allow participants in the training session to work in small groups and put into practice lessons learned using a fictional scenario. For this study, materials for the lecture and role-play exercise will be adapted and tailored to the stroke care context, including best practices in care planning as well as SDM [50].

From the patient’s perspective, a mix of home or rehabilitation center visits and telerehabilitation will be planned by the rehabilitation team for a maximum of 16 weeks. The rehabilitation services offered will be based on availability at each site. Evaluation, re-evaluation, and manual therapy treatments will be done face-to-face. To ensure internal validity, telerehabilitation sessions are expected to represent at least 80% of participants’ rehabilitation plans.

For each participant enrolled, at least one multidisciplinary meeting will be organized to present the rehabilitation treatment plan. The patient and family will participate in the meeting and the decision-making process using the telerehabilitation platform. The team will generate an interprofessional individualized treatment plan for each enrolled participant. A randomized sample of 60 meetings—30 from the control group and 30 from the intervention group—will be selected for recording. This type of nonparticipant observation will allow for a better understanding of the process of interprofessional SDM over the course of the trial.

### Primary Outcome

The choice of the primary outcome, patient adherence to the stroke rehabilitation plan at 12 weeks, was identified through a pilot study previously conducted by our research team as the most meaningful outcome and to better document the reason why telerehabilitation might be effective. Adherence to telerehabilitation has been operationalized in many different ways across studies [6,51]. We will define adherence as time spent (in minutes) doing any stroke rehabilitation exercises (online + offline). This includes, but is not limited to, physical, writing, and speech therapy as well as mental health–related exercises recommended by the rehabilitation professional. Online session time will be recorded through the telerehabilitation platform. Offline time will include face-to-face sessions doing rehabilitation as well as time exercising on one’s own as instructed by the rehabilitation professional. Offline sessions completed at home will be captured with the use of a journal and recorded by one of the rehabilitation professionals each week. This monitoring step has been used as a method of quality assurance by other scholars in stroke research [52]. Patients’ adherence to a rehabilitation program will also be measured by the Stroke Rehabilitation Exercise Adherence Measure (StREAM) questionnaire at weeks 4, 6 (to allow for test-retest reliability assessment), and 12 [53]. Moreover, health care professional perception of the participants’ adherence to the rehabilitation program will be evaluated on a numerical 10-point rating scale each week during the intervention period.

### Secondary Outcomes

Secondary clinical outcomes, the instruments used to measure them, and times of measurement are listed in Table 1 [46,54-63].

Focus groups will be conducted with 6 to 12 purposefully selected rehabilitation team members from each site at the end of the intervention phase. Stroke rehabilitation team members will be selected to capture a variety of professions and roles within the team and to ensure information-rich discussions. Themes such as the attributes of telerehabilitation, facilitating contextual conditions, opinion leadership, and platform adaptation for both clinical and collaborative work will be explored with patients and families as well as professionals. Quarterly in-depth interviews with the five site clinical champions will document their ongoing experience.

Similarly, qualitative interviews with 5 to 8 purposefully selected intervention patients and their families, when available, per site will further document the patients’ and families’ experiences of the technology, interprofessional SDM, and relationship with their outcomes.

**Table 1 table1:** Secondary outcomes.

Outcome		Instrument	Time of measurement
**Patients**			
	Reintegration into normal life	Reintegration to Normal Living Index [54]	Baseline and 12 weeks
	Ability to perform daily activities	Functional Independence Measure [46]	Baseline and 12 weeks
	Participation in shared decision making (SDM)	Questionnaire by Strull et al [55]	Following the establishment of the patient treatment plan
	Decisional conflict	SURE (Sure of myself; Understand information; Risk-benefit ratio; Encouragement) questionnaire [56]	Following the establishment of the patient treatment plan
	Satisfaction with treatment plan	Satisfaction with Decision scale [57]	Following the establishment of the patient treatment plan
	Depression	The Beck Depression Inventory [58]	Baseline, 12 weeks, and 24 weeks
	Satisfaction with health care received	Health Care Satisfaction Questionnaire [59]	12 weeks
**Health care use**			
		Institut national de santé publique du Québec population questionnaire (section A) [60]	12 and 24 weeks
		Provincial health administrative data	12 and 24 weeks
	Adverse events	Patient’s calendar (collected weekly by a rehabilitation professional): incidence of falls, dizziness, pain (visual analog scale), and fatigue (Borg Rating of Perceived Exertion Scale, 1-10)	Weekly basis up to 12 weeks
	Individual costs	Questionnaire developed by the authors for this study	24 weeks

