### Sample Size Estimates

We calculated the sample size for a univariate comparison of the primary outcome between the two study groups at 12 weeks. The required sample size was calculated using G*Power (version 3.1.9.4; Heinrich-Heine-Universität Düsseldorf) based on a conservative estimated effect size of the intervention (Cohen *d*) of 0.4. This sample size was calculated assuming the following: (1) a two-sided type I error probability of 5% and a power of 80%, (2) a duration of 12 weeks, (3) a 2:1 ratio of intervention to control group participants, (4) two study groups, (5) a <5% loss to follow-up, and (6) intracluster correlations of 0.10. Therefore, 330 participants will be recruited: 110 and 220 participants in the control and intervention groups, respectively.

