### Analyses

Baseline site and participant characteristics will be summarized descriptively. Patient outcomes will be summarized by group and site. Statistical analysis of the data will follow intention-to-treat principles. A linear mixed model will be used, with individuals’ data nested into a study site, to isolate the effect of the intervention on both clinical and process outcomes from other changes that may take place during the trial. Key contextual factors, such as patient’s sex and age, state of employment prior to stroke, stroke severity, concomitant rehabilitation treatments received outside the rehabilitation center, and time since stroke event (in days), will be considered in regression models as potential confounders. Interaction terms will be included in the model for any statistically significant contextual factors. Presence of dichotomous stroke outcomes (eg, dizziness) will be compared between study groups using a chi-square test. Multiple imputation will be considered if missing data represent more than 10% of a given variable. Sensitivity analysis will be conducted to assess the impact of missing data on estimates of intervention effects with a multiple imputation statistical technique and without imputation (ie, available case analyses), as well as for outlying observations.

Interviews and treatment plan meetings will be fully transcribed. A descriptive analytical approach will be used to develop a framework of organizational factors leading to a successful telerehabilitation intervention, both at the patient and professional levels. Audio recordings and transcripts will be reviewed simultaneously to assess validity of the transcription process and will be analyzed using an iterative approach [64]. Data saturation will be determined as defined by Constantinou et al [65]. This will be followed by an intersite analysis to identify what is common between the sites examined and what is specific to certain sites, and to compare the different configurations between sites. Finally, matrices with contextual factors will be generated to identify particular patterns [66].

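### Table 1 limits adverse events to four calendar items over 12 weeks, so emergency visits, admissions and deaths fall outside the stated harm comparison

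*Protocol article*

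**What the plan says.** The Objective in the protocol article's abstract lists two distinct secondary outcomes side by side: "adverse events related to telerehabilitation, use of services (up to 6 months").

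Table 1 gives each its own measurement.

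- **Adverse events.** The source is the patient's "calendar (collected weekly by a rehabilitation professional"). The content is "incidence of falls, dizziness, pain (visual analog scale), and fatigue (Borg Rating of Perceived Exertion Scale, 1-10"). The timing is "Weekly basis up to 12 weeks".
- **Health care use.** The sources are a population questionnaire and "Provincial health administrative data", both at 12 and 24 weeks.

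No row of Table 1, and no sentence under Primary Outcome or Secondary Outcomes, names emergency visits, admission, recurrent stroke or death.

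The Intervention Phase section allows a rehabilitation plan of up to 16 weeks and expects at least 80% of it to be delivered remotely.

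On analysis, the Analyses section states: "Presence of dichotomous stroke outcomes (eg, dizziness) will be compared between study groups using a chi-square test". On missing data it states: "Multiple imputation will be considered if missing data represent more than 10% of a given variable", and it plans sensitivity analyses with and without imputation. It does not say how to classify a patient whose calendar ends early.

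**The concern.** The article fixes the content, source and window of the outcome it calls adverse events. As fixed, that outcome covers symptoms a patient can write down at home and omits the serious end of harm.

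The source is also weakest where harm is greatest, because a patient who is admitted or dies will plausibly stop keeping the calendar. Such a patient's most important event has no field in the record, and the later weeks are blank.

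At stake is the reading of a secondary outcome, not of the primary one. If serious events differ between the control and intervention periods, the adverse-event comparison could show no difference, or a small one in the wrong direction. Any signal would have to be found in a different outcome that is not presented as harm.

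The window adds to this. It closes before the longest permitted rehabilitation plan ends, and well before follow-up of health care use ends.

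**Working it through.** The plan states no figure on this point, so there is none to reproduce. The check sets the provisions side by side and then illustrates the mechanism with assumed rates.

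**Content and window (Table 1; Intervention Phase)**

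| Item | Covers | Until |
|---|---|---|
| Adverse-event calendar | falls, dizziness, pain, fatigue | week 12 |
| Rehabilitation plan | treatment itself | up to week 16 |
| Health care use | questionnaire, administrative data | week 24 |

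- Treatment time with no adverse-event collection: 16 − 12 = up to 4 weeks.
- Health care use follow-up with no adverse-event collection: 24 − 12 = 12 weeks.

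**What happens when a calendar stops**

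The article leaves the classification open, so there are two cases.

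1. The patient is counted as event-free. The patient stays in the denominator with no event.
2. The patient is treated as missing. The patient leaves the available-case comparison, or is imputed from patients who went on keeping the calendar.

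In neither case is the admission or death scored as an adverse event.

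**Illustration (all rates assumed; none is in the documents)**

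Let *s* be the risk of a serious event, and *p* the risk of a calendar event in patients without one. For simplicity, suppose a patient with a serious event contributes no calendar event. Take *p* = 20% in both groups, *s* = 5% in control and *s* = 10% in intervention.

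| Scoring | Formula | Control | Intervention |
|---|---|---|---|
| Calendar only, counted event-free | p(1 − s) | 0.20 × 0.95 = 19.0% | 0.20 × 0.90 = 18.0% |
| Calendar only, excluded as missing | p | 20.0% | 20.0% |
| Serious events counted | p(1 − s) + s | 19.0% + 5% = 24.0% | 18.0% + 10% = 28.0% |

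A 4-point difference in one direction becomes a 1-point difference in the other, or none. With equal serious-event risks of 5% in both groups, the calendar shows 19.0% in each group and the full count 24.0% in each. The comparison is then unbiased, but the level of harm is understated.

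**Scale (assumed rates again)**

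The planned sizes are "110 and 220 participants in the control and intervention groups, respectively". For a serious-event risk between 2% and 20%:

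- control: 110 × 0.02 = 2.2 to 110 × 0.20 = 22 patients;
- intervention: 220 × 0.02 = 4.4 to 220 × 0.20 = 44 patients.

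These are patients with a serious event, not patients without any calendar event. Someone admitted after a fall may already have that fall in the calendar. The range shows orders of magnitude only.

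**The case against.** The strongest reply is that this is a condensed article. Serious-event definitions and reporting duties usually sit in the full protocol, and Table 1 does not say that no other harms are recorded. That stands as far as safety reporting goes: nothing here shows that the trial fails to record serious events. It does not answer the point about the outcome, because the article itself defines what the adverse-event outcome contains, and a reporting procedure elsewhere would not alter that definition.

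A second reply is that health care use is compared in its own right to 24 weeks, so admissions may well be reported by group. This also stands. Admissions are absent from the harm comparison, not necessarily from the trial. How health care use will be summarised is not stated.

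A third reply is that the stated outcome concerns events related to telerehabilitation, so counting every admission would widen it. That is a fair caution and the reason to label the added outcome all-cause. But the control phase contains no telerehabilitation, so relatedness to it cannot be judged in that group. A comparison between groups needs a definition that applies to both.

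Three stronger readings are tempting, and the documents do not support them.

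- **The trial already holds data showing readmission, recurrent stroke and death.** The article names the administrative data but not their contents. That they show admissions is a reasonable inference; diagnoses and deaths are undocumented.
- **Seriously harmed patients will be scored as event-free.** No passage says so. The calendar is gathered weekly, so a stop would probably be noticed, and the missing-data text could apply.
- **Safety equivalent to face-to-face care is one of the trial's questions.** The stated objectives concern clinical, process and cost outcomes and contextual factors. Adverse events are one secondary outcome among several.

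**Conclusion.** The point holds as a weakness in how the adverse-event outcome is defined. It is restricted to four calendar items over 12 weeks, against a plan of up to 16 weeks and health care use follow-up of 24 weeks. It contains no emergency visit, admission or death, and a calendar that ends through admission or death cannot record that event under either way of handling the patient.

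The number of patients affected cannot be derived from the documents, because no rate of serious events is given. The illustration shows that the definition can hide or reverse a difference, not that it will. It rests on assumed rates, on unequal serious-event risks between the groups, and on those patients having no earlier calendar event.

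The primary analysis is untouched. The change should be made, and there is time for it: the Results section says analysis will not start before data collection ends.

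**What to change.** 1. Confirm and state which fields the provincial administrative data and the service questionnaire contain: emergency visits, admissions (planned or unplanned), diagnoses, deaths.
2. Add to the adverse-event row of Table 1 an all-cause serious-event outcome, reported by group at 12 and 24 weeks: any emergency visit or unplanned admission, and death. Show fall or injury diagnoses and stroke diagnoses separately where the records allow.
3. Report the four calendar items beside it as diary symptoms up to 12 weeks.
4. State that a patient whose calendar stops because of admission or death is not scored as event-free.

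If the fields are present, the cost is wording and a few derived variables from sources already scheduled at 12 and 24 weeks, with no new patient contact. If a field is absent, death in particular, that component needs another source or must be declared unavailable. The downside is that some admissions unrelated to telerehabilitation will be included, so the outcome must be labelled all-cause and not read as attributable harm.

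### Health care use is scheduled only after enrolment and prior use is not a named confounder, so in this non-randomised before-after comparison a difference in prior use between phases may be mistaken for an effect on service use or cost

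*Protocol article*

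**What the plan says.** **Measurement times.** Table 1 of the protocol article gives two sources for health care use, a population questionnaire and "Provincial health administrative data". Each is timed at "12 and 24 weeks". In the same table, depression is timed at "Baseline, 12 weeks, and 24 weeks", and reintegration and functional independence are each taken at baseline and 12 weeks.

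**Role of the outcome.** The Objective in the abstract lists service use, followed for up to six months, among the secondary patient outcomes. The last paragraph of the Introduction makes cost part of the first specific objective.

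**Allocation.** Under Setting, each site first runs a usual-care period, and "Participants recruited during this period will belong to the control group". Of that period the article says "this is expected to take between 12 and 18 months". An intervention period with newly recruited patients follows.

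**Analysis.** Under Analyses, a linear mixed model with patients nested in site is meant "to isolate the effect of the intervention on both clinical and process outcomes from other changes that may take place during the trial". Sex, age, employment before the stroke, stroke severity, rehabilitation received elsewhere and time since stroke "will be considered in regression models as potential confounders". The list is given as examples, so it is open. It names neither prior health care use nor comorbidity.

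**The concern.** In a randomised trial, a missing pre-enrolment value for service use would cost mainly precision. Here the groups are consecutive cohorts, so it also bears on bias. Nesting patients in site deals with stable differences between sites. It does not deal with a change, within a site, in the kind of patient who enrols in each phase.

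Such a change is plausible, though not shown:

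- Under Intervention Phase, participants are expected to receive at least 80% of their plan by telerehabilitation. Those who accept this may differ from those who agreed to be followed in usual care.
- The phases are far apart in time. The Results section expects another 6 to 12 months of control data collection, then 2 to 3 years for the intervention group.

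At stake is any statement that telerehabilitation changes service use or cost. An open covariate list helps only if the variable exists, because a value that was never extracted cannot be adjusted for.

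**Working it through.** The article states no figure for health care use, so there is none to reproduce. The check has two parts.

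**1. Reading check**

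| Item | Where | Finding |
|---|---|---|
| Health care use, both sources | Table 1 | No pre-enrolment time point |
| Reintegration, function, depression | Table 1 | Baseline for all three |
| Allocation | Setting | By recruitment period, different patients |
| Prior use as a confounder | Analyses | Not named; list open |
| Dates covered by the administrative extract | – | Not stated |

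**2. Possible size**

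Inputs from Sample Size Estimates: 110 control and 220 intervention patients, two-sided 5% level. Inputs that are assumptions and not in the documents: δ, the difference in mean prior use between phases in SD units, and ρ, the correlation between prior and later use.

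- Bias of the phase contrast without adjustment: ρ × δ, in SD units of later use.
- Standard error of the contrast, ignoring site clustering: √(1/110 + 1/220) = √0.01364 = 0.117 SD.
- False-positive rate with no true effect, normal approximation: 1 − Φ(1.96 − bias/SE) + Φ(−1.96 − bias/SE).

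For δ = 0.2:

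- ρ = 0.3: bias = 0.2 × 0.3 = 0.06 SD; 0.06/0.117 = 0.51; false-positive rate 8.1%.
- ρ = 0.5: bias = 0.2 × 0.5 = 0.10 SD; 0.10/0.117 = 0.86; false-positive rate 13.7%.

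Over a wider range of assumptions (bias in SD, then false-positive rate):

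| δ | ρ = 0.3 | ρ = 0.5 | ρ = 0.7 |
|---|---|---|---|
| 0.1 | 0.03; 5.8% | 0.05; 7.1% | 0.07; 9.2% |
| 0.2 | 0.06; 8.1% | 0.10; 13.7% | 0.14; 22.4% |
| 0.3 | 0.09; 12.0% | 0.15; 25.0% | 0.21; 43.6% |

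These figures are before any other adjustment. Once the planned covariates are in the model, what counts is the imbalance and correlation that remain given those covariates, and both may be smaller.

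Adjustment for prior use would also reduce residual variance, to 1 − ρ². That is 0.91 at ρ = 0.3 and 0.75 at ρ = 0.5, equivalent to 1/0.91 = 1.10 and 1/0.75 = 1.33 times the patients for this outcome. The same caveat about the other covariates applies.

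**The case against.** **The article condenses a fuller plan.** For linked records, the listed times can be read as follow-up horizons, and the extraction window may be set in a full protocol or data-access request that is not shown. This stands in part: the article does not exclude a look-back. But it does fix a measurement schedule, and that schedule, like the named confounders, contains no prior use.

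**Service use has no true baseline.** Depression and function are states measured with the same instrument at enrolment and later. Service use accumulates over time, and use just before enrolment includes the stroke admission itself. This stands, so the contrast within Table 1 is not a contradiction. The useful variable is a separate covariate, use before the stroke.

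**Other planned features absorb part of the difference.** Age, stroke severity and prior employment may overlap with prior use, and the Study Design section says that the design accommodates existing trends. This also stands in part. A time trend can absorb gradual drift, but not a change in who enrols that coincides with the switch of phase. How much the covariates absorb is unknown.

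**The remedy is imperfect.** The two groups' look-back windows fall in different calendar periods, so prior use mixes patient differences with changes in service supply. This stands. Adjustment reduces confounding but does not remove it.

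**A stronger reading.** A reader might infer that differences in prior use will be reported as an effect, or that savings will be overstated. The documents do not support either. Bias requires that prior use differs between phases, that it predicts later use, and that the association survives the planned adjustment. None of these is shown, and no direction can be given. Nor do the documents state that the administrative source reaches back before enrolment or that consent covers it. Both are plausible and need confirmation.

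**Conclusion.** The point holds as a possible bias in a secondary outcome. As scheduled, health care use has no pre-enrolment value from either source and prior use is not a named confounder, while the comparison is between non-randomised, consecutive cohorts. A difference in prior use between phases may therefore be mistaken for an effect on service use or cost.

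Under an assumed 0.2 SD difference and a correlation of 0.3 to 0.5, the bias before other adjustment is 0.06 to 0.10 SD, and the false-positive rate is about 8% to 14% with 110 and 220 patients. Neither assumption comes from the documents, and the planned covariates would lower these figures by an unknown amount. The primary outcome, its sample size and its analysis are not affected.

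**What to change.** First confirm that the data access and the consent allow a look-back, including for patients already enrolled (37 by July 2021, according to Results). If they do:

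1. Extend the administrative extract to the 12 months before the stroke admission in both groups, so that the index admission is not counted.
2. Add *pre-stroke* to the Table 1 timing for the administrative source.
3. Report prior use by phase as a balance check.
4. Prespecify prior use as a covariate in the 12- and 24-week comparisons of use and cost.
5. Show these comparisons with and without the adjustment, because the look-back windows cover different calendar periods.

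The cost is a wider date range in the data-access request, matching ethics wording and one covariate. No added patient assessment is needed. Results says that analysis will wait until data collection ends, so the change can still be fixed before outcomes are examined. If a look-back is not permitted, the report should state that use and cost differences are not adjusted for prior use.
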